### Sample

Data are being gathered from two siblings and up to two parents in 712 families where children will be aged 11 to 16 at the launch of data collection and living in the continental United States, at least half time with their military parent since the deployment. Children each will have experienced the same parental wartime deployment lasting at least 90 days, prior to age 6 for at least one child. A spouse or partner presently living with the military parent will also be invited to participate; an average of 1.66 parents per family is anticipated. Over 1 million service member parents have been deployed to Iraq and Afghanistan since 2001; 33.5% of their children are in the targeted age range [5, 42], yielding an estimated maximum pool of more than 200,000 families after accounting for families with only one child.

Families are not being excluded by divorce so long as the participating children have lived at least half time with the military parent. Families will be excluded if there is an active ongoing investigation for family violence; if any of the prospective participants has a significant cognitive impairment that would prevent comprehending or responding to questions; if the military parent is deployed during the study period; if only one adolescent is willing to participate; or if the military parent does not fit within a stratum with unfilled spaces.

The sampling frame was constructed using probability methods from DoD personnel records by the Defense Manpower Data Center (DMDC) using information about family members in the Defense Enrollment Eligibility Reporting System (DEERS) and deployments in the Contingency Tracking System (CTS) and PERSTEMPO file. The sample was drawn to ensure representation of service branches, components (active or reserve), and paygrades (officer/enlisted) using a systematic sampling method. To compensate for their low representation in the military [43], female military parents were oversampled to comprise 65% of the sample using explicit stratification [42]. The sample also was stratified according to military parents’ exposure to adverse experiences, compensating for higher nonresponse typical of high risk groups. Based on national data, approximately half the military parents are expected to have experienced at least one of 12 adverse experiences prior to deployment [9]. Based on screening, each family is assigned to gender and risk groups as they enter the study. Interviewers are blind to participant risk group.

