## Abstract

Multiple adjustment difficulties have been associated with children’s exposure to recent parental wartime military deployments, but long-term consequences have not yet been systematically studied. This investigation will assess direct and indirect relationships between exposures to parental deployments early in life and later youth adjustment. Parents’ psychological health and family processes will be examined as mediators, and parents’ and children’s vulnerability and support will be examined as moderators. Archival data will be combined with new data gathered from two children and up to two parents in families where children will be aged 11 to 16 at the first data collection and will have experienced at least one parental deployment, for at least one child prior to age 6. Data are being gathered via telephone interviews and web-based surveys conducted twice one year apart. Outcomes are indicators of children’s social-emotional development, behavior, and academic performance. Notable features of this study include oversampling of female service members, inclusion of siblings, and inclusion of families of both veterans and currently serving members. This study has potentially important implications for schools, community organizations and health care providers serving current and future cohorts of military and veteran families.

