This study also is designed to permit consideration of both parent and youth sex as moderators of the relationships between early exposure to parental deployments and later youth adjustment. There are good reasons to expect that mothers’ deployments may be especially impactful or that boys and girls may be differentially vulnerable, but existing evidence is mixed.

Consistent with Masten and Narayan’s [39] recognition that the developmental timing of adverse experiences is consequential, deployments, life events, and other experiences will be coded in ‘child time’ (i.e., months since birth), including exposures occurring prenatally, as well as timing relative to deployment. More positive outcomes are expected when exposures began later and were less frequent or prolonged, and/or when parents experienced fewer traumatic experiences during deployment. The controlled heterogeneity of deployment timing in this study will help to provide greater clarity about the role of child age in these effects, thus addressing the lack of consistency in previous findings in relation to deployment effects.

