### Recruitment and consent procedures

After the sampling frame was received in the fall of 2020, public records searches were undertaken to verify and update addresses, and recruitment began, using evidence-informed procedures similar to those previously approved by regulatory authorities for use in studies of military populations (e.g., our preliminary studies, Millennium Cohort Study) [50].

Beginning in the spring of 2023, eligible participants received a series of communications: **A)** A printed postcard indicating that an invitation to participate will be coming; **B)** A hard-copy packet of recruitment materials including an invitation letter and a Frequently Asked Questions brochure inviting the military parent, his or her spouse, and two children to participate. If multiple children are eligible, the youngest two are invited to participate (to minimize the likelihood of ‘aging out’ or leaving home before the end of the study). Separate packets are included for spouses and children, along with a small preincentive [51]. Families are asked to indicate interest by calling an telephone number, sending email to a specified address, returning a reply card, or visiting a website; **C)** A series of email or postcard reminders that include links to the study website; and **D)** A limited sequence of telephone call attempts to invite participation and respond to questions.

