### Model building and estimation

Measurement models will be developed first, per the psychometric analyses. Latent variables will be used when computationally possible. Structural models will be built in stages paralleling study aims, assessing model fit to the data at each stage [112]. Analyses will be conducted using AMOS, Mplus 7 [111], STATA [113], and SAS [114]. Item-missing data will be handled using Full Information Maximum Likelihood (FIML) procedures available within Mplus and STATA [115]^.^ This approach is advantageous, as simulation studies have found it performs superior to listwise deletion and multiple imputation [116]. Sampling weighted estimation that corrects for unequal selection and non-response across strata will be used [107, 117]. In general, an alpha of 0.05 will be used to determine support or lack thereof for hypotheses. However, focus will be on effect size and confidence intervals for the distribution of effects [118].

A mixed-effects modeling approach to the multilevel, nested data structure will be used to explicitly estimate within- and between-family variability [119]. Change in children’s outcomes will be evaluated with two types of models: 1) Three-level mixed-effect models with time nested within child and siblings nested within families, where change is assessed using a predictor variable indicating baseline and follow-up time points, and interactions with the time variable test the effects of predictors on changes in outcomes; and 2) Two-level models with siblings nested in families that include autoregressive effects for each outcome (i.e., control for Time 1 levels), thus controlling for stable levels of each construct and testing effects on residualized change. Both approaches to modeling change provide rigorous inferences about the hypothesized relationships [120]. Models will control for: 1) parents’ age, education, and minority and employment status; 2) family type and size; 3) military branch and paygrade. Sensitivity analyses will be conducted to ensure that these controls do not obscure important findings. Strategies for analyzing each aim are described below.

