#### Analyses for aim 1: To assess direct relationships between the timing, frequency, duration and content of siblings’ early exposures to parental deployments and later youth adjustment

Maladjustment is hypothesized to be greater for children whose exposures began earlier (operationalized as child age at first deployment, including gestational age, coded from archival data), were more frequent (i.e., total number of deployments during the child’s lifetime) prolonged (i.e., total days deployed), ended more recently (i.e., days since end of most recent deployment), or who were exposed to deployments where parents’ experiences were more traumatic (i.e., total scores on self-report Combat Exposure items). These hypotheses will be tested using a SEM framework, where a series of path models will estimate the direct effects of deployment characteristics on each indicator of adjustment. Paths from the independent variables will be tested concurrently, thus establishing the unique association for each deployment risk factor. Interactions between different deployment components—frequency, duration, timing, and content—will also be examined to determine whether long-term effects of deployment are exacerbated or mitigated for various deployment combinations. Within-family comparisons will be conducted to determine whether these direct effects differ across siblings.

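### The shared-deployment rule ties age at first deployment to being the older of the sampled pair, and the listed controls include neither sibling position nor child age

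*Protocol article*

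**What the plan says.** All references are to the protocol article.

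- **Eligibility (Sample).** "Children each will have experienced the same parental wartime deployment lasting at least 90 days, prior to age 6 for at least one child". The pair is drawn from a narrow age window: "children will be aged 11 to 16 at the launch of data collection". Recruitment and consent procedures adds: "If multiple children are eligible, the youngest two are invited to participate".
- **Timing predictor (Analyses for aim 1).** Timing is "operationalized as child age at first deployment, including gestational age, coded from archival data". The hypothesis is that earlier first exposure goes with worse adjustment. Frequency, total days deployed, time since the last deployment and combat exposure enter the model at the same time.
- **Controls (Model building and estimation).** "Models will control for: 1) parents’ age, education, and minority and employment status; 2) family type and size; 3) military branch and paygrade". The sensitivity analyses promised there ask whether these controls hide findings, not whether one is missing.
- **Use of siblings (Analyses for aim 1).** "Within-family comparisons will be conducted to determine whether these direct effects differ across siblings". The model section says of the design: "The controlled heterogeneity of deployment timing in this study will help to provide greater clarity about the role of child age in these effects". The introduction and the Innovation section present the sibling design as a way to separate child-specific factors from deployment and parental ones.

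**The concern.** The eligibility rule restricts who can have a late first exposure. The younger child of a pair always met the shared deployment before age 6, so late first exposures occur only among older siblings. Age at first deployment therefore runs together with being the older of the two.

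Nothing in the control list separates them. Family type and size are the same for both siblings, and parent and military variables are shared or nearly so. Older and younger siblings may differ in adjustment for reasons unrelated to deployment. Part of any such difference would then load on the timing coefficient. If older siblings fare better, this would mimic the hypothesized effect; if they fare worse, it would mask it.

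The problem is sharpest where the article expects most of its design. In a pair that shares all its deployments, number of deployments, days deployed, recency and parental combat exposure are the same for both children. Timing is the only deployment predictor that differs within the pair, and it differs by exactly the age gap.

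**Working it through.** **1. Deduction from the rule.** Let the shared deployment fall at date D, with birthdates b_older < b_younger. The rule needs min(D − b_older, D − b_younger) < 6 years. The smaller value is D − b_younger, so the younger child was under 6 at D and the younger child's first exposure is before 6. A child first exposed at 6 or later is therefore the older one. If D is the first deployment for both, the difference in timing is (D − b_older) − (D − b_younger) = b_younger − b_older, the age gap.

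**2. The plan's own benchmark.** Table 1, child-level predictor, repeated measures: effective n = 2492/(1 − 0.30) = 3560. Detectable beta = (1.960 + 0.842)/√3560 = 2.8016/59.67 = 0.047, as stated.

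**3. Correlation of timing with position.** The article gives no distribution of deployment dates or numbers, so these are assumed. Sibling pairs aged 11 to 16 and at least 9 months apart were given random deployment dates and kept if they met the Sample rule.

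| Deployments, at most | Eligible pairs | Younger sibling first exposed at 6+ | Correlation of timing with being older |
|---|---|---|---|
| 1 | 59,535 | 0 | 0.499 |
| 2 | 78,361 | 0 | 0.395 |
| 4 | 102,306 | 0 | 0.268 |

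Other assumed patterns (spacing uniform over 1 to 5 years, varying shares of pairs with an earlier deployment) widen the range to about 0.26 to 0.58.

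**4. False beta, pooled.** Assume no true timing effect and an older/younger difference of d SD. Half the children are older siblings, so position has SD 0.5 and the false beta is d × 0.5 × r.
- d = 0.1, r = 0.26: 0.013
- d = 0.2, r = 0.58: 0.058

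**5. False beta, family random intercept, ICC 0.30.** This is closer to the planned mixed model. The within-family share of timing variance is w = pooled beta / pure within-pair beta. The random-intercept beta is the within-pair beta × [w/0.7] / [w/0.7 + (1 − w)/1.3]. At d = 0.2:
- at most 1 deployment: w = 0.0499/0.1595 = 0.313; 0.1595 × 0.447/(0.447 + 0.528) = 0.073
- at most 2: w = 0.0395/0.1291 = 0.306; 0.1291 × 0.437/(0.437 + 0.534) = 0.058
- at most 4: w = 0.0268/0.0883 = 0.304; 0.0883 × 0.434/(0.434 + 0.536) = 0.040

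At d = 0.1 these halve, to 0.037, 0.029 and 0.020. The range is about 0.02 to 0.07.

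**6. Effect of adding current age.** The pooled false beta falls to about 0.005 to 0.02. It does not reach zero, because position is a step that age captures only in part.

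**7. Cost of adding position.** Variance inflation is 1/(1 − r²): 1.07 at r = 0.26 and 1.51 at r = 0.58. Detectable beta = 0.047 × √inflation: 0.049 and 0.058.

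Steps 4 to 7 treat timing without the other deployment predictors, so they indicate size only.

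**The case against.** **The planned predictor is continuous.** A reader might infer that the study compares early-exposed children with a later-exposed group made up wholly of older siblings. The article plans no before-6 versus 6-and-over contrast. Many older siblings were also first exposed before 6, so timing and position are correlated, not inseparable. This objection stands and limits the point to partial confounding.

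**Within-pair estimates.** A reader might also take the pure within-pair false betas (0.09 to 0.16 at 0.2 SD in the simulation above) as the size of the problem. The stated sibling comparison tests whether effects differ across siblings; it is not described as a within-pair estimate of the timing effect. Table 1's detectable values are not computed for such an estimator either. Those betas serve here only as an intermediate step. Testing whether effects differ across siblings is still not an adjustment for position.

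**The size is assumed.** The article gives no older/younger difference and no direction. At 0.1 SD every false beta above lies below 0.047, and all are small beside the 0.18 to 0.32 that the article cites for deployment duration and trauma. This stands.

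**Birth order.** Because the two youngest eligible children are invited, the older of the pair need not be the firstborn. The rule fixes position in the pair only.

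**Looser abstract.** The abstract says that children "will have experienced at least one parental deployment, for at least one child prior to age 6", without requiring the same deployment for both. With several deployments, that wording would admit some younger siblings first exposed at 6 or later. The Sample section is the operative eligibility text, and the point rests on it.

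**A condensed article.** Child-level covariates are often left to a fuller plan, and their absence alone would be no finding. Here the article fixes an eligibility rule and an explicit control list, then claims a separation of factors that the two together do not deliver.

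**Conclusion.** The point holds as partial confounding. Under the Sample rule, any child first exposed at 6 or later is the older of the pair. Age at first deployment correlates with position at about 0.26 to 0.58, depending on assumed deployment patterns. Followed as written, the control list lets an older/younger difference enter the Aim 1 timing coefficient. With an assumed difference of 0.1 to 0.2 SD, the false beta is about 0.01 to 0.06 pooled and 0.02 to 0.07 with a family random intercept. It reaches the detectable 0.047 only toward the upper end of those ranges. Current age, which is not listed, would remove more than half of the pooled bias but not all of it.

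The deduction needs only the eligibility wording; the magnitudes rest on the assumed deployment dates, spacing and position difference. The documents do not support saying that the timing effect cannot be estimated, or that the bias must favor the hypothesis.

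**What to change.** In Model building and estimation, and in the Aim 1 analyses, add two child-level controls: position in the sampled pair (older or younger) and child age at interview. Age needs the qualification that it be estimable. In a family with a single deployment it equals age at first deployment plus days deployed plus days since the deployment ended, all of which are already in the model. It then has to be identified from families with several deployments, or one term has to be dropped and the choice stated.

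Add one sentence saying that, in pairs sharing their first deployment, a within-pair timing difference cannot be separated from sibling position or the age gap.

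Both variables come from birthdates already requested from DEERS, so no new data are needed. The cost is a slightly wider interval for the timing effect: position alone inflates its variance by about 1.1 to 1.5, which moves the detectable repeated-measures beta from 0.047 to about 0.049 to 0.058.

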### Sample size determination with statistical power calculation

Data will be obtained from 712 families at baseline, with 2 children and up to 2 parents per family (given divorce rates, 1.66 parents per family are estimated). Stratification will be used to over-select female service members and high-risk families such that 456 families will have female military parents and 356 families will be high risk. Power is calculated for three types of analytic samples:

A baseline/cross-sectional analysis sample of 712 families and 1,424 children (2 per family), and 1,182 parents (1.66 per family);A panel analysis sample composed of families who participate at both waves of the study. Based on experience and other military studies [44], 75% retention is projected, resulting in 534 families, 1,068 children, and 887 parents at Wave 2;A repeated measures sample, comprising all observations from both waves. With a 75% family retention rate, the sample will include 1,246 (= 712 + 534) repeated family observations and 2,670 repeated child observations, and 2,216 repeated parent observations. The repeated measures sample will be the priority sample for testing study hypotheses.

Effective sample sizes are calculated for a two-level, mixed-effects model per Snijders [45] using an estimated within-family ICC = 0.30. Power is estimated for a standardized regression coefficient in a model with 5 covariates and alpha = 0.05. Effect sizes detectable at .80 power are listed in Table 1.

**Table 1 pone.0295007.t001:** Detectable effect sizes.

Direct, Moderation, and Mediation Effects (n = cross-sectional / panel / repeated)	Detectible Standardized Beta		
	Cross- sectional	Panel	Repeated Measures
**1. Family level predictors** (n = 712 / 534 / 1246; effective n = 1095 / 822 / 1917)	0.085	0.098	0.064
**2. Child level predictors** (n = 1424 / 1068 / 2492; effective n = 2034 / 1526 / 3560)	0.063	0.072	0.047

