#### Analyses for aim 2: To assess the role of parents’ psychological health and family processes in mediating relationships between siblings’ early exposures to parental deployment and later youth adjustment

This aim highlights four indirect pathways through which deployment(s) influence youth adjustment. Deployment factors studied in Aim 1 are expected to be negatively related to parents’ psychological health, parental efficacy, marital relationship quality, and family functioning at Time 1, which in turn will be positively related with youth adjustment at Time 2. The magnitude and statistical significance of the indirect effects of deployment through each of these processes will be tested using the INDIRECT command within Mplus, which employs a product of coefficients method of testing mediation [121] and the bootstrap method to compute standard errors for the significance test [122]. Importantly, the four indirect pathways will be tested concurrently, highlighting not only which pathways are critical for understanding the potential enduring effects of parental deployments on youth adjustment, but also the relationships among them. Differences across siblings also will be assessed.

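### Aim 2 relates Time 1 mediators to Time 2 adjustment, so Table 1's panel column fits it, not the repeated measures column given priority

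*Protocol article*

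**What the plan says.** The section on sample size and power describes three analytic samples: a baseline sample, a panel of families seen at both waves, and a repeated measures sample that pools both waves. For the panel, "75% retention is projected, resulting in 534 families, 1,068 children, and 887 parents at Wave 2". For the pooled file, "the sample will include 1,246 (= 712 + 534) repeated family observations and 2,670 repeated child observations". It then states: "The repeated measures sample will be the priority sample for testing study hypotheses". No aim is exempted.

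Table 1 gives detectable betas in one column per sample. Its heading covers direct, moderation and mediation effects, and the text below it says that rows 1 and 2 apply to the Aim 2 mediation effects.

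The section on analyses for Aim 2 expects the deployment factors to be negatively related to four mediators "at Time 1, which in turn will be positively related with youth adjustment at Time 2". It does not say whether Time 1 adjustment is controlled on the mediator-to-adjustment path.

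The section on model building and estimation plans two models of change: a three-level model with time within child within family, and a two-level model with siblings within families that controls the Time 1 level of the outcome. It assigns neither to an aim.

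**The concern.** The priority sentence and the Aim 2 definition do not fit together. A Time 1 mediator related to Time 2 adjustment uses only Wave 2 outcomes. The Wave 1 outcomes that enlarge the pooled file have no earlier measured mediator and add nothing to that path. A reader who takes the priority sentence at its word will read the Aim 2 detectable effect from the wrong column.

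The inference is also at stake. Parents' symptoms, family functioning and youth adjustment can plausibly influence each other. The 12-month lag gives some protection against reading a youth-to-parent effect as mediation, but a lag alone does not remove it. The Time 1 level of adjustment must also be in the model, and the Aim 2 section does not say that it is.

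**Working it through.** **Inputs**, all from the power section and Table 1:

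- "Power is estimated for a standardized regression coefficient in a model with 5 covariates and alpha = 0.05". Sidedness is not stated; two-sided reproduces the table.
- "Effect sizes detectable at .80 power are listed in Table 1".
- "Effective sample sizes are calculated for a two-level, mixed-effects model per Snijders [45] using an estimated within-family ICC = 0.30".
- Child observations in Table 1: 1,424 cross-sectional, 1,068 panel, 2,492 repeated. The last is 2 × 1,246. The text gives 2,670 instead; I use the table's number because it reproduces the table's results.

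**Step 1: reproduce Table 1.** Effective n is child observations/(1 + ICC) for family-level predictors and child observations/(1 − ICC) for child-level predictors. Detectable beta is (1.960 + 0.842)/√(effective n) = 2.802/√(effective n).

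| Column | Level | Effective n | Beta, computed | Beta, printed |
|---|---|---|---|---|
| Repeated | family | 2,492/1.3 = 1,917 | 0.0640 | 0.064 |
| Repeated | child | 2,492/0.7 = 3,560 | 0.0470 | 0.047 |
| Panel | family | 1,068/1.3 = 822 | 0.0977 | 0.098 |
| Panel | child | 1,068/0.7 = 1,526 | 0.0717 | 0.072 |

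All 12 effective sample sizes in Table 1 reproduce, and all 12 betas agree to within 0.002.

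**Step 2: which column fits Aim 2.** The mediator-to-adjustment path needs a Wave 1 mediator and a Wave 2 outcome, so it rests on 534 families and 1,068 children. Even if full-information maximum likelihood keeps Wave 1-only families for the deployment-to-mediator path, that path has at most 712 families, the cross-sectional column (0.085 / 0.063). The repeated measures column describes neither path.

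**Step 3: size of the gap.** 0.098/0.064 = 1.53 and 0.072/0.047 = 1.53, so the applicable betas are 53% larger.

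**Step 4: power at panel size for the repeated measures betas.** Power = Φ(beta × √(effective n) − 1.960).

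- Family: 0.064 × √822 = 1.835; Φ(−0.125) = 0.45.
- Child: 0.047 × √1,526 = 1.836; Φ(−0.124) = 0.45.

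These are figures for one path coefficient, as everywhere in Table 1, and not for the product that Aim 2 tests.

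**Step 5: why the Time 1 control matters.** Suppose the only effect runs from youth adjustment to the mediator, with standardized size r at Time 1, and youth adjustment has 12-month stability s. Neither value is in the article. By path tracing, the lagged path without Time 1 adjustment is r × s, and with Time 1 adjustment controlled it is 0 (assuming linearity and no measurement error in Time 1 adjustment). For r = 0.3 and s = 0.6 the uncontrolled lagged path is 0.18. Holding r at 0.3, it runs from 0 at s = 0 to 0.30 at s = 1, and it exceeds the panel's detectable 0.098 once s passes 0.098/0.3 = 0.33. The controlled path is 0 throughout.

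**The case against.** The strongest reply is that the article already contains the right pieces. The panel column is printed beside the repeated measures column, the Aim 2 section is explicit about time order, and the model-building section plans a model that controls Time 1 levels. A specific analysis section would normally govern a general remark in a power section, and priority does not exclude other samples. Which model serves which aim is also a detail that an article may leave to the full protocol.

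Much of this stands, and it rules out three stronger readings.

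- **That the quoted power does not apply to Aim 2 at all, or that Aim 2 is underpowered.** Only the repeated measures column misses. The panel betas of 0.098 and 0.072 remain below the 0.10 that the article cites as small and well below its cited 0.18 to 0.32. Those cited values are deployment effects on youth outcomes rather than mediator paths, but nothing here shows a shortfall against them.
- **That the article prescribes mediation with mediator and outcome from the same occasion.** It names a sample and describes no such test.
- **That most pooled observations have no time order.** By outcome wave, 1,424 of 2,492 child observations (57%) are Wave 1. Counted by child, 2,136 of 2,492 (86%) come from children seen twice. Deployment dates come from records. Only the order of mediator and outcome is in question.

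The reply does not remove the mismatch itself. The priority sentence is unqualified, the table is applied to mediation without saying which column, and the Aim 2 section's time order cannot be met by the sample given priority.

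**Conclusion.** The point holds in limited form. The sample named as priority for the study hypotheses does not match the Aim 2 test as defined. The single-path detectable betas for the mediator-to-adjustment path are 0.098 and 0.072, not 0.064 and 0.047; at panel size the smaller values have about 45% power. This rests on the article's own ICC of 0.30, 75% retention, two-sided alpha of 0.05 and Table 1's observation counts. The possible bias from an uncontrolled lagged path rests on assumed values and illustrates why the model choice matters; it does not estimate the bias in this study.

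**What to change.** In the power section, limit the priority of the repeated measures sample to direct effects. There and in the Aim 2 section, name the panel sample and the two-level autoregressive model, with Time 1 adjustment controlled, as primary for the mediator-to-adjustment path. In the Aim 3 section, say the same for the conditional indirect effects. Quote the panel column of Table 1 for Aim 2. Treat any indirect effects from pooled same-occasion data as secondary.

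The cost is wording; no new data are needed. The stated detectable effect for Aim 2 becomes less favourable. Controlling Time 1 adjustment also narrows the question to further change over 12 months, so any mediated effect already present at Time 1 is not counted on this path. The text should say so.
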